## Abstract

**Background:** Sarcopenia (loss of muscle mass) and dynapenia (loss of strength) are prevalent in older adults aged 70 years and over. Both have an impact on their functional ability and quality of life, with type II muscle fibres being particularly affected. Although traditional resistance training (TRT) is effective, it presents technical difficulties and an increased risk of injury among this vulnerable population. Isometric strength training (IST) is a potentially safer, more accessible and more effective alternative. **Objective:** To describe the protocol of a single-arm, pre-post intervention trial designed to evaluate the efficacy and applicability of a 16-week IST programme on muscle strength, skeletal muscle mass, quality of life and applicability (safety, acceptability, perceived difficulty) in 18 older adults aged 70 years and above with a diagnosis of sarcopenia and dynapenia. The influence of genetic and environmental factors on the variability of response to IST will also be explored. **Methodology:** The participants, who have all been diagnosed with sarcopenia according to EWGSOP2 (European Working Group on Sarcopenia in Older People 2) criteria, will perform two IST sessions per week for 16 weeks. Each 30-min session will consist of one progressive set (total duration 45 s to 90 s) for each of the eight major muscle groups. This series will include phases at 20% and 40% of individual Maximal Voluntary Isometric Contraction (MVIC), culminating in 100% Maximal Effort (ME), using the CIEX SYSTEM machine with visual feedback. The primary outcome variables will be: change in knee extensor MVIC and change in Appendicular Skeletal Muscle Mass Index (ASMMI). Secondary variables will be measured (other components of sarcopenia, quality of life by EQ-5D-5L, use of Likert scales, posture and physiological variables), and saliva samples will be collected for exploratory genetic analyses. The main statistical analyses will be performed with *t*-tests for related samples or their non-parametric analogues. **Discussion:** This protocol details a specific IST intervention and a comprehensive evaluation plan. The results are expected to provide evidence on the feasibility and effects of IST among older adults with sarcopenia and dynapenia. Understanding individual variability in response, including genetic influence, could inform the design of more personalised and effective exercise strategies for this population in the future.

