#### 2.2.1. Study Outcome Variables (Outcomes)

The following variables will be assessed at pre- and post-intervention (week 0 and week 17, unless otherwise stated) to determine the efficacy and applicability of the IST, as distinguished from the eligibility measures (Section 2.1.1):A.Primary Outcome Variables (Assessment of reversal of dynapenia and sarcopenia):
1.Change in MVIC Knee Extensors:○Specific measurement variable: MVIC of the knee extensors, measured in Newtons (N) with the CIEX SYSTEM machine.○Analysis metric: Absolute change (MVIC_week17_–MVIC_week0_)○Method of aggregation: Mean and Standard Deviation (SD) of the change. The percentage change will also be calculated.○Time point(s): Baseline (week 0) and post-intervention (week 17) assessments.○Clinical Relevance: Knee extensor strength is key to functionality and independence in older adults; its improvement indicates reversal of dynapenia.2.Change at ASMMI:○Specific measurement variable: ASMMI (ASMM in kg/height^2^ in m^2^), measured by bioimpedance (InBody 230).○Analysis metric: Absolute change (ASMMI_week17_–ASMMI_week0_)○Method of aggregation: Mean and SD of change.○Time point(s): Baseline (week 0) and post-intervention (week 17) assessments.○Clinical Relevance: Fundamental diagnostic criterion for sarcopenia (EWGSOP2); an increase indicates improvement in the amount of muscle, essential for metabolic health and reduced frailty.
B.Secondary Outcome Variables

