#### 2.3.1. Sample Size Calculation

The sample size was determined after an internal pilot study (N = 50) conducted by the research team (Baigene), using a similar training protocol (CIEX SYSTEM machine) but without visual strength feedback. It was carried out in a population aged ≥65 years with and without sarcopenia/dynapenia and had a duration of 10 weeks. The primary variable for calculation was quadriceps MVIC (N). Pilot results (mean ± SD, Pre vs. Post):Left quadriceps: 224.78 ± 64.49 N vs. 296.55 ± 89.38 N; Cohen’s d (paired samples) = 1.22.Right quadriceps: 263.53 ± 84.66 N vs. 306.24 ± 106.74 N; Cohen’s d (paired samples) = 0.51. Effect sizes were calculated with the mean and SD of the pre-post differences. Given the expected greater improvement with feedback in this protocol, the more specific population (≥70 years with sarcopenia/dynapenia) and the longer duration of the current intervention, a (conservative) d = 0.80 was adopted for the calculation. With G*Power v3.1.9.7, for a related samples *t*-test, detecting d = 0.80 with 80% power and α = 0.05 (bilateral) requires N = 15. Adjusting for 15% losses, 18 participants will be recruited, an adequate number for this pilot exploratory study.

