#### 2.3.2. Analysis Strategy

Primary and secondary quantitative variables will be compared pre-post with Student’s *t*-tests for related samples, after testing for normality (Shapiro-Wilk). If the data are not normally distributed or contain outliers, non-parametric tests (e.g., the Wilcoxon signed-rank test) will be employed. Effect sizes (Cohen’s d) and confidence intervals will be calculated. Multivariate analyses will include a multiple linear regression to explore the influence of genetic and environmental variables on strength and muscle mass improvement, with Bonferroni correction for genetic analyses. Qualitative variables (e.g., sarcopenia diagnosis) will be analysed by using McNemar tests. Applicability variables (Likert scales, adverse events) will be analysed with descriptive statistics and *t*-tests or Wilcoxon tests for pre-post comparisons on Likert scales. Additionally, exploratory subgroup analyses will be performed to assess whether the response to IST on primary variables differs according to sex, age ranges (70–79 vs. ≥80 years) and baseline severity of sarcopenia/dynapenia. Adjustment for baseline covariates will be considered in regression models. The software will be IBM SPSS v29.0 and R v4.3.1.

For the assessment of the secondary hypotheses concerning the applicability (Section 2.2.2) of the IST protocol, specific analyses will be carried out:

Hypothesis H1 (low injury risk): This will be assessed through two approaches. First, Adverse Events (AEs) will be recorded (including their type, severity, and causality), and ‘low risk’ will be inferred if the incidence of IST-related injuries is minimal and comparable to or lower than rates reported in the literature for strength training in older adults [1,33,34,35]. Second, Perceived Safety will be measured post-intervention using a 5-point Likert scale; the approach for this subjective scale is based on similar methods used in previous research [87]. The hypothesis will be supported by a mean score of ≥4.

Hypothesis H2 (high acceptance): This will be assessed by: (1) compliance rate, with a success threshold of ≥90% of completed sessions, and (2) a satisfaction score from a 5-point Likert scale administered post-intervention, using a validated measurement approach [88]. The hypothesis will be supported by a mean satisfaction score of ≥4.

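### Two unranked primary outcomes, a sample size justified for only one of them, and no statement of how the two results together decide the main hypothesis

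*Protocol article*

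**What the plan says.** - **Two primaries.** The Abstract states: "The primary outcome variables will be: change in knee extensor MVIC and change in Appendicular Skeletal Muscle Mass Index (ASMMI"). Section 2.2.1 lists the same two as items 1 and 2 under the heading "Primary Outcome Variables (Assessment of reversal of dynapenia and sarcopenia"), with no order of importance.
- **Sample size.** Section 2.3.1 states: "The primary variable for calculation was quadriceps MVIC (N"). It reports pilot paired effects of 1.22 (left quadriceps) and 0.51 (right), and then "a (conservative) d = 0.80 was adopted for the calculation". The result is "detecting d = 0.80 with 80% power and α = 0.05 (bilateral) requires N = 15", raised to 18 for 15% losses. No effect size, standard deviation or power is given for ASMMI.
- **Analysis.** Section 2.3.2 compares all primary and secondary quantitative variables before and after by paired t-test, or Wilcoxon where the data require it. The only correction stated is "with Bonferroni correction for genetic analyses".
- **Decision rule.** Sections 2.2.2 and 2.3.2 set numerical thresholds on the Likert scores for H1 to H3. The main hypothesis, in the Introduction, covers both sarcopenia and dynapenia and has no rule linking it to the two primary tests.

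**The concern.** With two primary tests, the meaning of a positive trial depends on how they are combined. If one significant result is enough, two unadjusted tests give the main hypothesis two chances of a false positive. If both are required, the power that matters is the chance that both are significant, and the planned 80% covers only one of them. The stated 0.05 and the stated 80% both describe the MVIC test alone, and the protocol does not say which combination applies. The choice should be made before data are seen, particularly as section 2.1.5 says that assessors cannot be fully blinded to time point.

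**Working it through.** **Inputs.** From 2.3.1: paired t-test, d = 0.80 for MVIC, two-sided α = 0.05, 80% power, N = 15, 15% losses, 18 recruited. Assumed: 0.05 for each primary test (2.3.2 gives no level), and a range of ASMMI effects, since the protocol gives none.

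**Step 1: reproduce the plan's figure.** Power is the probability that a noncentral t with n − 1 degrees of freedom and noncentrality d√n falls outside ± the t critical value.
- n = 14, d = 0.80: 79.0%.
- n = 15, d = 0.80: 82.1%. So N = 15 is right.
- 15 / 0.85 = 17.6, rounded up to 18, also right.

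**Step 2: either outcome suffices.** For independent tests the family-wise error is 1 − (1 − 0.05)² = 1 − 0.9025 = 9.75%. For correlated, jointly normal statistics it is 9.5%, 9.1% and 8.3% at correlations 0.3, 0.5 and 0.7. The bound with no assumption about dependence is 0.05 + 0.05 = 10%.

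**Step 3: both required.** The error for the joint claim is at most 5%. Joint power cannot exceed the smaller of the two powers. If the tests are independent it is their product. With MVIC at d = 0.80:

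| Assumed ASMMI d | ASMMI power, 15 completers | ASMMI power, 18 completers | Joint power, 15 completers, independent |
|---|---|---|---|
| 0.2 | 11% | 13% | 9% |
| 0.3 | 19% | 23% | 16% |
| 0.4 | 30% | 36% | 25% |
| 0.5 | 44% | 52% | 36% |
| 0.6 | 58% | 67% | 48% |
| 0.8 | 82% | 89% | 67% |

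The last joint figure is 0.821 × 0.821 = 0.67. If all 18 complete, it is 0.892 × 0.892 = 0.80. The smallest ASMMI effect with 80% power is d = 0.78 for 15 completers and 0.70 for 18. With d = 0.80 for both outcomes and independence, 80% joint power needs 19 completers, and 19 / 0.85 = 22.4, so 23 recruited.

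**Step 4: compare remedies for MVIC at d = 0.80 and 15 completers.**
- Bonferroni at 0.025 each: MVIC power falls from 82.1% to 71.7%. Restoring 80% needs 18 completers, and 18 / 0.85 = 21.2, so 22 recruited.
- Fixed sequence, MVIC then ASMMI, each at 0.05: MVIC power stays at 82.1%. The family-wise error is at most 5%. If the MVIC null is true, any false claim first requires a false MVIC rejection (5%). If it is not, only the ASMMI test can err (5%).

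**The case against.** The strongest reply has four parts.

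- **Status.** Sections 2.1 and 2.3.1 call the trial exploratory and a pilot, and section 4 presents it as a step before a randomised trial. Strict family-wise control matters less here. This stands and lowers the weight of the point. It does not remove it, because the protocol keeps an efficacy hypothesis, named primaries and a formal power calculation.
- **A separate analysis plan could hold the testing rule.** This is fair for the hierarchy alone. The sample-size calculation, however, is fixed in this document and covers one of two equal primaries.
- **The 9.75% need not apply.** The main hypothesis joins sarcopenia and dynapenia, which suggests that both are needed, and 2.2.1 ties each outcome to its own construct, which suggests two separate claims. A reader might infer that the trial's error rate is 9.75%. The documents do not support that: nowhere do they say that either result alone suffices, and 0.05 per test is inferred from the sample-size section.
- **ASMMI may be adequately powered.** A reader might infer that the ASMMI test is shown to be underpowered. It is not. The protocol gives no ASMMI effect, and at d = 0.80 its power would be 82%. Nor would a non-significant ASMMI result be uninterpretable, since 2.3.2 plans effect sizes and confidence intervals.

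It is also true that 2.3.1 openly names quadriceps MVIC as the variable used for the calculation. What it leaves unsaid is what that implies for the other primary outcome.

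**Conclusion.** The point holds in a conditional form and is modest. The two consequences are alternatives and do not add up. If either outcome alone counts as support, the family-wise error is up to about 9.75% under independence, and lower with positive correlation. If both are required, the error is controlled, but the 80% no longer describes the chance of success. Joint power is then capped by ASMMI power, and with 15 completers is about 67% even when both effects are 0.80 and independent.

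These figures assume 0.05 per test, paired t-tests and, for ASMMI, effects that are not in the protocol. If the two outcomes are meant as separate claims, each keeps its own 5% level, but the protocol would need to say so, because its main hypothesis covers both.

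**What to change.** - **Section 2.3.2:** state a fixed sequence. Knee-extensor MVIC is tested first at two-sided 0.05. ASMMI is tested at 0.05 only if MVIC is significant, and is otherwise reported as an estimate with its 95% confidence interval.
- **Section 2.3.1:** add that the 80% power covers MVIC only, and that with 15 completers ASMMI has 80% power for d of about 0.78 (0.70 with 18).

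This takes two sentences, adds no participants and costs MVIC no power. MVIC goes first because the trial is already sized on it.

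The cost is that ASMMI cannot be claimed on its own if MVIC is not significant. The chance of an ASMMI claim becomes the joint power: at an assumed ASMMI d = 0.5, 36% instead of 44% with 15 completers under independence. Requiring both, or naming a single primary, would also be valid if it suits the aims better. Requiring both would need an ASMMI effect in the sample-size calculation.

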## 1. Introduction

Ageing brings with it biological changes which, even in the absence of disease, lead to a progressive loss of muscle mass (sarcopenia), strength (dynapenia) and musculoskeletal function [1]. Sarcopenia has been defined by the European Working Group on Sarcopenia in Older People (EWGSOP) [2,3] as low muscle mass and strength and/or poor physical performance. It has a prevalence of 1–29% in older adults and may exceed 50% in institutionalised populations or those with comorbidities [1,2,4]. Dynapenia (loss of strength) often precedes sarcopenia, has a greater impact on functional ability, and is a robust predictor of falls, disability and mortality [1,2,4]. This muscle loss, which begins as early as age 30, accelerates after age 60 [5], with muscle tissue decreasing by 2.1% per year from age 50, while strength decreases by 1.5% (50–60 years) and up to 3% thereafter [6]. These processes are linked to impaired protein synthesis [7,8,9], chronic inflammation [10] and muscle disuse [1]. As a consequence, there is a reduction in physiological resilience, quality of life and mobility. This is coupled with an increased risk of falls [1], diabetes [11], osteoporosis [12] and cognitive impairment [13,14,15], which can lead to growing levels of morbidity and mortality.

Physiologically, sarcopenia and dynapenia mainly affect type II (fast) muscle fibres [16,17,18]. Their loss is associated with hormonal declines (testosterone, GH, IGF-1) [19,20,21] and increased inflammatory cytokines (TNF-α, IL-6), which contribute to systemic inflammation and muscle degeneration [18,20,22]. Strength training (ST) is a key tool to prevent muscle inactivity, sarcopenia and dynapenia [1,23,24], improving not only physiological frailty but also physical function, mobility, independence, chronic disease management, psychological well-being and quality of life [23,25,26].

Stimulation of type II fibres is crucial, but requires high intensities of effort [27,28,29,30]. Traditional resistance training (TRT), while effective when following recommended guidelines (2–3 sets of 6–12 repetitions at 70–85% of 1 RM, performed 2–3 times per week) [1] and incorporating proposed power exercises (using moderate loads at high speeds, typically 40–60% of 1 RM), presents certain challenges: high-threshold motor units are only activated near muscular failure [31,32], which increases the risk of compensatory movements and potential injuries [1]. In addition, high-speed, moderate-load exercises require high technical control and may injure various joints [33,34,35].

In this context, isometric strength training (IST) is a valuable alternative, used in rehabilitation, physical training and special populations [36,37,38,39]. Maximal voluntary isometric contraction (MVIC) is a reliable measure of health and sports performance [39,40,41]. IST has been shown to be effective against sarcopenia and dynapenia, inducing improvements in strength and hypertrophy [42,43,44,45]. Movement intention can be as effective as contraction velocity in improving Rate of Force Development (RFD) [39,46], and mechanical strain at maximal IST can exceed that of maximal concentric actions [36,47], optimising stimulation of high-threshold fibres.

There are mainly two types of isometric action: Pushing Isometric Muscle Action (PIMA) (push/pull against immovable resistance) and Holding Isometric Muscle Action (HIMA) (static load maintenance) [48]. Variations of IST include modification of joint angles [39,49,50], intensity or duration of contraction [39,51,52]. PIMA at Long Muscle Length (LML) appears to maximise mechanical tension [37,53] and promote early activation of high-threshold motor units [46,54]. Training at LML has shown superiority for hypertrophy and changes in muscle architecture (increased fascicle length) [44,50,55]; in fact, training at LML and Middle Muscle Length (MML) generates greater improvements than at Short Muscle Length (LMS) [44,45,50]. IST protocols of longer duration (e.g., 4 × 30 s) also appear to induce greater hypertrophy than those of shorter duration (e.g., 4 × 10 × 3 s) with equal time under tension [51]. In addition, IST allows controlled, pain-free work, preventing injury [36,37,39,56] and having acute analgesic effects [57,58] mediated by corticomotor pathways [38]. Thus, IST is a viable and safe alternative to TRT in older adults, although its efficacy may vary on an individual basis.

The variability in response to training and progression of sarcopenia may be partially explained by genetic factors. Previous studies have associated polymorphisms with sarcopenia (ACTN3; MTHFR; NRF2) [59,60], muscle hypertrophy (TGFβ; Myostatin, GDF-8) [61,62] and response to ST (ACTN3, ACE, NOS3, PPARGC1A/B, VEGFA) [63,64,65,66,67,68,69]. Analysing these factors together with others related to inflammation (CRP, IL6) [70,71], oxidative damage (SOD2, CAT, GPX), cell damage/regeneration (CASP, MMP3, GDF5, TNC) [71,72,73] and nutrigenomic factors (FAP2, ADBR, UCP2, GCKR, ADCY5, GIPR, HFE, TF) [74,75,76] could help to understand variability following the proposed intervention.

Considering the impact of sarcopenia/dynapenia, the difficulties of TRT and the potential of IST, there is a clear need to design and rigorously evaluate specific and optimised IST protocols for older adults, investigating their efficacy and applicability, as well as the influence of individual factors.

Therefore, the main research question that this protocol seeks to address is whether a 16-week IST programme can be an effective, safe and applicable intervention to counteract sarcopenia and dynapenia and improve quality of life in older adults, and to explore the individual factors that modulate response. Although IST is generally considered safe, potential discomfort or adverse events will be carefully monitored, as detailed in the methodology section (see Section 2.2.2 on safety assessment).

Consequently, the main objective of this study is to design an intervention protocol to evaluate the effect of 16 weeks of IST on sarcopenia, dynapenia and quality of life among adults aged 70 years and above. In addition, the influence of genetic and environmental variables on the variability of response to IST will be analysed in order to optimise its applicability and efficacy in this population group.

With a view to meeting the main objective of the study, a protocol is proposed to achieve the following strategic objectives:To assess the reduction of sarcopenia and dynapenia by increasing muscle mass and strength following the application of an IST protocol in older adults.To analyse the improvement in quality of life following the application of the IST protocol.To assess the applicability of the IST in terms of safety for, and acceptability and perceived difficulty by older adults.To determine the influence of genetic factors on the response to IST, considering variables related to muscle type, fibre damage and regeneration, vascularisation, inflammation, resistance to oxidative damage, and fat and carbohydrate metabolism.

The main hypothesis of the study is that the IST represents a highly effective choice for the reduction of sarcopenia and dynapenia, contributing to the improvement of health and quality of life among older adults. In addition, the following secondary hypotheses are proposed:

 **H1.**
*IST has a low risk of injury in older adults.*

 **H2.**
*IST increases the acceptance of strength training by older adults.*

